### Eligibility criteria {10}

#### Inclusion criteria for subjects

Patients meet the diagnostic criteria of NERD in guide and TCM with cold-heat complex syndrome at the same time.18–65 years old.Those who did not receive similar drugs (PPI, H2 receptor antagonist, gastric mucosal protective agent, etc.) within 2 weeks before the trial.Voluntarily participated in this study and signed the informed consent form (ICF).

#### Exclusion criteria

Patients with reflux esophagitis, reflux hypersensitivity (RH), or Barrett esophagus (BE).Patients with a disease history of upper gastrointestinal bleeding or surgery, esophageal stricture, esophageal and gastric tumors, and other organic diseases.Patients with serious primary diseases, such as cardiovascular, cerebrovascular, liver, kidney, and hematopoietic systematic diseases.Taking other drugs or treatments related to NERD (PPI, H2 receptor antagonist, gastric mucosal protective agent, etc.) within 2 weeks.Women who are breastfeeding, during pregnancy, or preparing for pregnancy.Patients with anxiety or depression.Patients with a history of mental ill or neurological diseases or language disorders.Allergic constitution or being allergic to the known ingredients of the drug in the study.Currently participating in other clinical trials.

#### Inclusion criteria for healthy subjects

Those who have no typical clinical symptoms of NERD such as acid regurgitation, heartburn, and reflux.The score of GERD-Q scale < 8 points.18–65 years old.Those who voluntarily participate in this study and sign the ICF.

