### Participants

We aim to recruit patients who have typical gastroesophageal reflux symptoms (such as acid reflux and heartburn), or who do not have typical gastroesophageal reflux symptoms, but have 24-h impedance-pH monitoring showing that they are related to gastroesophageal reflux. The symptoms above are not less than three months, and the gastroscopy show nonerosive gastroesophageal reflux. The inclusion criteria of TCM refers to the diagnosis of cold-heat complex syndrome in the “consensus on Integrated traditional Chinese and Western Medicine diagnosis and treatment of gastroesophageal reflux Disease” issued by the Digestive Professional Committee of the Chinese Society of Integrated traditional Chinese and Western Medicine in 2017 (Table 2). The inclusion criteria of western medicine is based on the consensus of experts on gastroesophageal reflux disease issued in 2014 (Table 3). And we will also recruit 10 healthy subjects for control.

**Table 2 Tab2:** Diagnostic criteria for cold-heat complex syndrome of NERD

Category	Symptoms or signs
Main symptom	Burning discomfort in the retrosternal or epigastric region. Anti-acid or spitting clear water. Dull pain in the epigastric stomach, like warming, and pressing. Fasting stomachache, relieved by eating.
Minor symptoms	Loss of appetite; Fatigue; Thin stools; Lukewarm hands and feet.
Tongue	Red tongue, White fur
Pulse condition	Weak pulse

**Table 3 Tab3:** Inclusion criteria of NERD

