Those who have the typical clinical symptoms of NERD, such as heartburn and reflux, persist or recur for more than 3 months, and the above symptoms have a negative impact on the quality of life of the patients. Those who have atypical or extraesophageal symptoms, such as epigastric pain, abdominal distension, belching, non-cardiogenic chest pain, pharyngitis, cough, asthma, or foreign body sensation in the throat, which persist or recur for more than 3 months, the above symptoms have a negative impact on the patient’s quality of life: mild symptoms ≥ 2 days in a week, or moderate and severe symptoms ≥ 1 days in a week. Reflux diagnostic questionnaire (RDQ) scale symptom score ≥ 12, which is for diagnosis of reflux diseases in the China gastroesophageal reflux Research Cooperation Group. Those who have no esophageal mucosal lesions and Barrett esophageal manifestations by gastroscopy. Tweny-four-hour esophageal impedance-PH monitoring: impedance records showed reflux events. At the same time, symptom association probability (SAP) is used to determine the relationship between symptoms and reflux. If SAP > 95%, symptoms will be considered related to reflux.	

Diagnostic criteria: 1&3&4 or 2&4&5

The main symptom 1 or 2 is necessary. Patients with two main symptoms + either of the other one or two minor symptoms + appropriate tongue and pulse condition can be diagnosed as cold-heat complex syndrome

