#### Exclusion criteria for healthy subjects

Those who have been diagnosed as esophageal diseases such as NERD, RH, and BE.Patients with organic lesions such as upper gastrointestinal bleeding or operation, esophageal stricture, esophageal, and gastric tumors.Patients with serious primary diseases such as cardiovascular, cerebrovascular, liver, kidney, and hematopoietic system.Women who are breastfeeding, pregnant, or preparing for pregnancy.Patients with anxiety or depression.Those who with a history of mental or neurological disorders/diseases.Patients who have participated in any other clinical trials within 3 months.

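### The healthy-control criteria do not screen for the atypical symptoms through which the protocol itself recognises NERD, so an undiagnosed atypical case can enter the 10-person reference group

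*Protocol article*

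**What the plan says.** **Healthy controls.** Under Inclusion criteria for healthy subjects, the symptom criterion is "Those who have no typical clinical symptoms of NERD such as acid regurgitation, heartburn, and reflux". The same list requires "The score of GERD-Q scale < 8 points", an age of 18 to 65 and consent. Under Exclusion criteria for healthy subjects, the protocol removes "Those who have been diagnosed as esophageal diseases such as NERD, RH, and BE" and "Patients with organic lesions such as upper gastrointestinal bleeding or operation, esophageal stricture, esophageal, and gastric tumors". It also removes serious primary disease, pregnancy or breastfeeding, anxiety or depression, mental or neurological disorders, and recent participation in another trial. The written control criteria call for no gastroscopy and no impedance-pH test.

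**Patients.** The Participants section accepts people with typical reflux symptoms, "or who do not have typical gastroesophageal reflux symptoms, but have 24-h impedance-pH monitoring showing that they are related to gastroesophageal reflux". Table 3 sets this out as "Diagnostic criteria: 1&3&4 or 2&4&5". Item 2 begins "Those who have atypical or extraesophageal symptoms, such as epigastric pain, abdominal distension, belching, non-cardiogenic chest pain, pharyngitis, cough, asthma". It also asks for persistence or recurrence beyond 3 months, an effect on quality of life and a minimum weekly frequency. Item 4 is a gastroscopy without mucosal lesions or Barrett changes. Item 5 is impedance-pH monitoring, with the rule "If SAP > 95%, symptoms will be considered related to reflux".

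**Use of the controls.** The mechanistic outcome and the Statistical analysis section use the 10 healthy subjects, sampled once at baseline, as the non-disease reference for flora and metabolites.

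**The concern.** Patients may enter without typical symptoms, but the symptom question put to controls covers typical symptoms only. The disease exclusion covers only conditions someone has already diagnosed. The definition of healthy therefore leaves uncovered a part of what the protocol itself counts as NERD.

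At stake is the healthy-versus-NERD part of the mechanistic outcome. A control with unrecognised NERD moves the reference mean towards the patients, makes true disease differences look smaller and can change which flora and metabolites are picked as differential. With 10 controls, one such person is a tenth of the reference group.

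**Working it through.** **1. Can an undiagnosed atypical case pass the control criteria?** Take a volunteer who meets Table 3 item 2 (for example belching and distension for over 3 months, above the frequency threshold and affecting quality of life) and who has never been investigated.

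| Control criterion | Does it remove this volunteer? |
|---|---|
| No typical symptoms | No: the symptoms are atypical |
| GERD-Q below 8 | Not necessarily: it removes only those who score 8 or more |
| No diagnosed oesophageal disease | No: nothing has been diagnosed |
| No upper-GI organic lesion | No: item 4 requires a clear gastroscopy |
| No serious primary, mental or neurological disease | No |

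The volunteer qualifies. If investigation would have met items 4 and 5, this is a NERD case by the 2&4&5 route.

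Table 3 itself does not rely on a questionnaire score on this route. The score (item 3, RDQ of 12 or more) belongs to the typical route, and impedance-pH testing takes its place on the atypical one.

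**2. Effect of k such controls among 10.** Let H be the true healthy mean and P the patient mean for one feature. If misclassified controls have the patient mean:

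- control mean = [(10 − k)H + kP] / 10
- expected difference = P − control mean = (1 − k/10)(P − H)

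The difference is 90%, 80% and 70% of its true size for k = 1, 2 and 3. If such a control lies only a fraction r of the way from H to P, the loss per control is r × 10%.

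**3. How likely is at least one?** The documents give no prevalence. For an assumed share p of otherwise eligible volunteers, the chance is 1 − (1 − p)^10:

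- p = 5%: 40%
- p = 10%: 65%
- p = 20%: 89%

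Here p must be the share with true NERD, not with symptoms. If 10% to 20% had symptoms and a quarter of those had reflux (both assumed), p is 2.5% to 5% and the chance is 22% to 40%.

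**4. Illustration of power.** The protocol gives no calculation for the 10 controls. Its figure for patients reproduces: 2 × 0.766 × 0.234 × 2.8² / 0.308² = 29.6, rounded to 30, and 30 × 1.2 = 36 per arm. Assume a true 1 SD difference in one feature, 36 patients of one arm against 10 controls, and a two-sided 5% test.

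- Standard error = √(1/10 + 1/36) = 0.357
- Power = Φ[(1 − k/10)/0.357 − 1.96]
- Result: 0.80, 0.71, 0.61 and 0.50 for k = 0, 1, 2 and 3

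The non-central t gives 0.78, 0.69, 0.59 and 0.48. These figures show direction and scale only, because the effect size, k and full resemblance are all assumed.

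**The case against.** The strongest case on the other side has five parts.

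- **Other screens exist.** A reader might infer that controls are screened only for typical symptoms. That is not so: the GERD-Q cut-off and a list of disease exclusions also apply. None of them asks about item 2 symptoms, so the gap remains, but it is smaller than that reading suggests.
- **Atypical symptoms alone are not NERD.** A reader might infer that Table 3 diagnoses NERD from item 2 by itself. It does not: a clear gastroscopy and a symptom association probability above 95% are also required. Many volunteers with belching or distension would not have NERD, and the share with symptoms overstates the share misclassified.
- **Patients also need the cold-heat syndrome.** Main symptom 1 or 2 is mandatory, meaning retrosternal or epigastric burning discomfort, or regurgitation of acid or clear water. A person with belching alone could not be a trial patient. This brings patients closer to the typical picture that controls must lack. It does not close the gap, because burning in the epigastric region satisfies main symptom 1 and is not among the examples in the control criterion.
- **The size is assumed.** Prevalence, effect size and full resemblance are not in the documents, and a single-feature 5% test does not represent a search across many features. This objection stands in full.
- **Functional gut complaints.** One might want all functional gastrointestinal disease excluded. The documents do not show that such complaints move flora towards the NERD pattern, and nothing in them promises controls free of every gut complaint. That wider exclusion is closer to a preference.

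**Conclusion.** The point holds as a mismatch between the control criteria and Table 3. The protocol recognises NERD without typical symptoms, yet its control criteria neither ask about atypical symptoms nor test for reflux. An undiagnosed item 2 volunteer with GERD-Q below 8 counts as healthy.

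Each such control who truly has NERD and resembles the patients costs about 10% of the expected contrast. The frequency is unknown, so no overall bias or loss of power can be claimed.

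A reader might also infer that the trial's efficacy result is at risk. The documents do not support that: GERD-Q and the other efficacy outcomes, safety and the within-arm before-and-after flora comparisons do not use the healthy group. This is a cheap improvement to an exploratory comparison that is nonetheless one of the trial's stated aims.

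**What to change.** Replace the first healthy-subject inclusion criterion with one tied to Table 3: neither item 1 (typical) nor item 2 (atypical or extraesophageal) symptoms, as defined there, over the last 3 months.

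Ask any control already enrolled the same questions. Present the healthy-versus-NERD flora and metabolite comparison with and without those who fail.

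The cost is one changed line, a short symptom question for 10 people and a few more volunteers to screen. The randomized comparison and its analysis are unchanged.

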### Combined use of drugs {11d}

During the study period, drugs with the same efficacy as the study drugs or related to the treatment of NERD will be prohibited to reduce intervention. If the subjects take drugs to control chronic diseases, such as hypertension and diabetes, they should truthfully and detailedly record the medication in the trial, including drug name (or other treatment name), dosage, frequency, and time of use.

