(4)Mechanistic outcome: The samples will be used to study the composition structure and metabolite expression profile of intestinal flora in NERD patients through 16s rRNA sequencing and metabonomic association analysis in TCM group, western medicine group at baseline and week 8, and in normal subjects at baseline. By analyzing the correlation between a variety of differential flora and differential metabolites, we will demonstrate the effects of changes in the structure of intestinal flora on metabolic phenotypes and functional metabolic small molecules. This experiment attempts to screen some key strains through visual tools, further explore their mechanism in the pathogenesis of NERD, identify the advantages of treatment, and reveal the potential mechanism of HWJNR. The determination of intestinal flora and metabolites will be performed by Shanghai OE Biotech Co., Ltd (Shanghai, China).(5)Follow-up recurrence index: The number and percentage of the subjects with non-medication, maintenance medication, intermittent medication, and on-demand medication will be recorded at month 1 and month 3 respectively.

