### Statistical analysis {20}

Efficacy analysis will be performed based on both FAS and PPS patients. Safety analysis includes all randomized participants who take at least one bag of HWJNR and have data for safety assessment. Comparing the healthy control group with the traditional Chinese medicine group, we will study the composition of the intestinal flora and the expression of metabolites in patients with NERD and the healthy group. And it will also reveal the mechanism of action and advantages of HWJNR in the treatment of NERD patients.

Changes from baseline to post-treatment in GERD-Q, SF-36, PRO, and syndrome score of TCM will be analyzed using analysis of covariance with associated 95% confidence intervals. All the analysis results will be generated by SPSS 25.0 software. Repeated measurement data are expressed by mean ± standard deviation, intra-group comparison is performed by analysis of variance of repeated measurement data, and inter-group comparison is by multivariate analysis of variance (MANOVA). *P* ≤ 0.05 indicates that the difference is statistically significant. Unilateral test will be used in all statistical tests, and the significance level *P* ≤ 0.05. The arithmetic mean, standard deviation, median, minimum, and maximum will be calculated according to the data distribution. Counting data will be used to calculate the number and percentage of cases.

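### Healthy controls have no counterpart to the patients' 2-week acid-suppressant washout, so the exploratory healthy-versus-patient flora and metabolite contrast is open to bias from unequal drug exposure

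*Protocol article*

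**What the plan says.** **Patients.** The washout is stated twice in the protocol article. The inclusion criteria for subjects admit "Those who did not receive similar drugs (PPI, H2 receptor antagonist, gastric mucosal protective agent, etc.) within 2 weeks before the trial", and the exclusion criteria bar "Taking other drugs or treatments related to NERD (PPI, H2 receptor antagonist, gastric mucosal protective agent, etc.) within 2 weeks".

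**Healthy controls.** The inclusion list has four items: no typical reflux symptoms, "The score of GERD-Q scale < 8 points", age 18–65 and consent. The exclusion list covers diagnosed esophageal disease, organic upper-gastrointestinal lesions, serious primary disease, pregnancy and breastfeeding, anxiety or depression, mental or neurological history, and "Patients who have participated in any other clinical trials within 3 months". Neither list mentions a drug.

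**During the study.** Under Combined use of drugs {11d}, "drugs with the same efficacy as the study drugs or related to the treatment of NERD will be prohibited to reduce intervention". Medication for chronic disease is to be recorded. Antibiotics and probiotics are named nowhere in the article.

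**Use of the samples.** Fecal flora and metabolites are to be measured in the TCM group, "western medicine group at baseline and week 8, and in normal subjects at baseline" (Secondary outcome measurements, item 4). Statistical analysis {20} states: "Comparing the healthy control group with the traditional Chinese medicine group, we will study the composition of the intestinal flora and the expression of metabolites". It mentions no adjustment for drug exposure.

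**The concern.** The healthy-versus-patient contrast is not randomised. Eligibility is the only protection against drug exposure that the article describes for it, and on acid suppressants and related drugs the two sides have different rules. A volunteer taking a PPI can be symptom-free and score below 8 on GERD-Q because of the drug, so these two criteria do not screen for its use.

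At stake is how a flora or metabolite difference between controls and patients is read. The plan would attribute it to NERD. Part of it could instead come from drugs that some controls were taking and that patients had stopped. Omeprazole is the trial's comparator, so a PPI-using control would bring one of the exposures under study into the reference group.

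**Working it through.** The number of controls, 10, is given under Sample size {14} without a calculation, so there is no figure of the plan to reproduce on this point. The check is a side-by-side reading followed by an illustration under stated assumptions.

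**1. Criteria side by side**

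| Exposure | Patients | Healthy controls |
|---|---|---|
| PPI, H2 antagonist, mucosal protectant, similar drugs | None for 2 weeks (stated twice) | No criterion |
| Antibiotics, probiotics | No criterion | No criterion |
| Diagnosed esophageal disease | NERD required; reflux esophagitis, reflux hypersensitivity and Barrett esophagus excluded | Excluded |

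Only the first row is unequal in drug terms. The third row narrows the gap, because people treated for known reflux disease are already out of the control group. What remains is use without an esophageal diagnosis: self-medication, or use for another reason.

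**2. Chance that exposed controls enter**

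The documents give no rate, so p, the share of otherwise eligible controls with recent exposure, is an assumption. With 10 controls:

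- P(at least 1) = 1 − (1 − p)^10
- P(at least 2) = 1 − (1 − p)^10 − 10p(1 − p)^9

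| Assumed p | At least 1 of 10 | At least 2 of 10 |
|---|---|---|
| 5% | 40% | 9% |
| 10% | 65% | 26% |
| 20% | 89% | 62% |

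These are chances of contamination. They do not measure bias. Because of the diagnosis exclusion, the lower rows should not be taken as likely.

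**3. What contamination would do**

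Let f be the exposed fraction of controls and D the shift, in SD units, that the drug causes in one flora or metabolite measure. With no exposed patients at baseline, the control mean, and so the contrast, moves by f × D.

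| Exposed controls | f | D = 0.5 | D = 1.0 |
|---|---|---|---|
| 1 of 10 | 0.1 | 0.05 SD | 0.10 SD |
| 2 of 10 | 0.2 | 0.10 SD | 0.20 SD |
| 3 of 10 | 0.3 | 0.15 SD | 0.30 SD |

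For scale, the true difference detectable with 80% power at two-sided 5%, for a single measure with no multiplicity adjustment, is (1.96 + 0.84) × √(1/10 + 1/n). That is 1.00 SD against the 36 patients of the TCM group, 1.02 SD against 30, and 0.95 SD against all 72. The possible bias is thus well below what the contrast could reliably detect, but it falls on the one group with no replicate.

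**4. Which comparisons are touched**

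The two arms share one washout rule and are randomised. Their between-arm comparison, and each arm's change from baseline to week 8, use no data from healthy controls. GERD-Q at week 8 uses none either. Only contrasts that include the healthy group are exposed to the asymmetry.

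**The case against.** **The typical PPI user is already excluded.** This largely stands. Exclusion of diagnosed esophageal disease removes the most obvious route into the control group. It does not remove people who take these drugs without that diagnosis.

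**The contrast is exploratory.** This stands. It is one use of a mechanistic outcome listed fourth among the secondary measurements, and it has no sample-size claim.

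**A condensed article may leave sampling conditions to the full protocol.** This has force for antibiotics and probiotics, which a stool-sampling procedure may cover. It has less force for the washout. The article sets out separate eligibility lists for both groups, goes as far as a 3-month other-trial rule for controls, and states the washout twice for patients and not at all for controls.

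**Stronger readings that the documents do not support.** A reader might infer that the comparison is confounded. Actual exposure is unknown, so it is only open to bias. A reader might also treat the silence on antibiotics and probiotics as a confounder. That silence is the same for both groups: it adds noise, and it biases the contrast only if use differs between patients and controls, of which there is no evidence. Finally, a reader might extend the point to the estimated effects of HWJNR or omeprazole. The between-arm comparison does not depend on how controls were selected.

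**Conclusion.** The asymmetry is real and plainly stated: patients have a 2-week drug criterion and healthy controls have none. It leaves the exploratory healthy-versus-patient flora and metabolite contrast open to bias in a reference group of 10. Under the assumed shifts of 0.5 to 1.0 SD, one to three exposed controls would displace the control mean by 0.05 to 0.30 SD. Neither the number exposed nor the shift can be taken from the documents, and the direction of any bias is unknown.

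The severity is minor. The primary outcome, safety and the randomised contrasts stand as they are. The case for acting is that the remedy already exists in the patient criteria and costs almost nothing.

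**What to change.** 1. Add to the healthy-control criteria the 2-week drug criterion already used for patients, for controls still to be recruited. Trial status reports 10 volunteers recruited at submission but does not say whether any were controls, so the number this can cover is unknown.
2. In all groups, record antibiotic and probiotic use before each stool sample, over a look-back period that the investigators fix in advance. Without a fixed period, exposure is undefined.
3. Keep all samples in the main between-arm analysis and add a sensitivity analysis without exposed samples. Dropping exposed week-8 samples from the main analysis would condition on drug use after randomisation, which treatment may influence, and would weaken the randomised comparison.

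The cost is slightly narrower control recruitment, two CRF questions and one extra analysis. The sensitivity analysis will rest on fewer samples, which matters most among the 10 controls.

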Through the single-center, randomized, double-blinded, placebo-controlled clinical research, this trial aims to evaluate the efficacy and safety of HWJNR in patients with NERD (cold-heat complex syndrome). In addition, this trial intends to reveal the underlying pathogenesis by observing the effects of changes in intestinal bacteriocyte structure on metabolic ideotypes and functional metabolic small molecules.

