## Methods/design

### Study design and setting {8-9}

This is a single-center, double-blinded, placebo-controlled, randomized controlled trial (RCT), which will be conducted in Dongfang Hospital, Beijing University of Chinese Medicine. The study is conducted in accordance with the Declaration of Helsinki (Edinburgh 2000 version). The final protocol (Version 2.0, 11 November 2020) of this trial has been approved by Ethical Committee of Dongfang Hospital, Beijing University of Chinese Medicine (Version number: JDF-IRB-2020033602). In addition, this trial has been registered in the Chinese Clinical Trial Registry (No. ChiCTR2000041225, registered on 22 December 2020).

We aim to enroll 72 patients with NERD over a 2-year period (Date from November 2020 to December 2022) from the department of gastroenterology in Dongfang Hospital, Beijing University of Chinese Medicine. Eligible patients will be randomized at a ratio of 1:1 to either TCM group (HWJNR with omeprazole enteric-coated tablets placebo) or western medicine group (omeprazole enteric-coated tablets with HWJNR placebo) for 8 weeks treatment. At the end of this trial, the primary outcome (GERD-Q) and the secondary outcome (SF-36, PRO, syndrome score of TCM) will be evaluated. We will obtain peripheral venous blood, urine, and stool from NERD patients before and after treatment. This study involves 3 site visits (week 0, week 4, and week 8) and 10 call visits (weekly call during the treatment period and follow-up at month 1 and month 3). The process of the study is schematically shown in Fig. 1. And we will additionally recruit 10 healthy controls.

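### The 10 healthy controls are not balanced against the patients on age or sex, so the NERD-versus-healthy flora and metabolite differences may be confounded, with little precision to adjust afterwards

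*Protocol article*

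**What the plan says.** All references are to the protocol article.

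- **Number of controls.** The study design section states "And we will additionally recruit 10 healthy controls", and the sample size section repeats this. Neither gives a calculation for the 10.
- **Who may be a control.** The inclusion criteria for healthy subjects require no typical reflux symptoms, consent, and "The score of GERD-Q scale < 8 points.18–65 years old". The exclusion criteria for healthy subjects begin with "Those who have been diagnosed as esophageal diseases such as NERD, RH, and BE" and go on to organic lesions, serious primary disease, pregnancy or breastfeeding, anxiety or depression, mental or neurological disorders, and recent trial participation.
- **Who may be a patient.** The age limits are the same: "at the same time.18–65 years old.Those who did not receive similar drugs". The recruitment section names the hospital's digestive outpatients as the source of cases. No source is named for controls.
- **How the controls are used.** Under Statistical analysis: "Comparing the healthy control group with the traditional Chinese medicine group, we will study the composition of the intestinal flora and the expression of metabolites". The mechanistic outcome samples both treatment arms at baseline and week 8, and controls once. It then correlates differential flora with differential metabolites to screen key strains.
- **Adjustment.** Analysis of covariance is stated for GERD-Q, SF-36, PRO and the TCM syndrome score. None is stated for flora or metabolites.

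No section mentions matching, or any balancing of controls to patients on age or sex.

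**The concern.** Randomisation makes the two treatment arms comparable with each other. It does nothing for patients against healthy volunteers. That contrast is observational, and a shared range of 18 to 65 years (47 years wide) does not make the two age distributions alike: ten volunteers in their twenties would meet every listed criterion.

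If a bacterial taxon or metabolite varies with age or sex, and the controls differ from the patients in age or sex, that taxon or metabolite can appear as a NERD difference. It would then enter the set of differential features on which the mechanistic interpretation is built. With only 10 controls, there is limited room to separate the two explanations afterwards.

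**Working it through.** **Inputs from the document.** Controls: 10. Patients: 36 in the TCM group (the sample size section's 30 per group, raised by 20%: 30 × 1.2 = 36), or 72 if both arms are pooled at baseline. The document gives no precision or power figure for the controls, so there is none to reproduce.

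**Assumptions (not in the document).** One feature at a time, standardised to SD 1; two-sided 5% test; normal approximation; no multiplicity correction. The age gap *d* (in SD), the feature–age correlation *r*, and R² (the share of patient/control status explained by age and sex) are all assumed.

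**Step 1. Standard error of the mean difference.** SE = √(1/10 + 1/n).
- n = 36: √0.1278 = 0.357
- n = 72: √0.1139 = 0.337

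**Step 2. False-positive rate with no disease effect.** Bias = r × d. Rate = P(|Z + bias/SE| > 1.96).

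| d (SD) | r | Bias (SD) | n = 36 | n = 72 |
|---|---|---|---|---|
| 0.5 | 0.2 | 0.10 | 5.9% | 6.0% |
| 0.5 | 0.5 | 0.25 | 10.8% | 11.5% |
| 1.0 | 0.3 | 0.30 | 13.4% | 14.4% |
| 1.0 | 0.5 | 0.50 | 28.8% | 31.6% |

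Example, third row, n = 36: 0.30/0.357 = 0.84; P(Z > 1.96 − 0.84) + P(Z < −1.96 − 0.84) ≈ 0.131 + 0.003 = 0.134. The Statistical analysis section says all tests are one-sided at 0.05. On that rule, with the bias in the tested direction, this row becomes 21% to 22%.

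**Step 3. How much imbalance chance alone would give.** Suppose controls and patients came from one population.
- Mean age gap above 0.5 SD: probability 0.16 (n = 36) or 0.14 (n = 72).
- Mean age gap of 1 SD or more, n = 36: 1/0.357 = 2.80, probability about 0.5%.
- Share of women differing by 20 points or more, if the true share is 50%: 0.28 (n = 36) or 0.25 (n = 72).

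Gaps of 0.5 SD are therefore plausible by chance. Gaps of 1 SD would need volunteers to be drawn from a different age group.

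**Step 4. What adjustment would cost.** Detectable difference at 80% power = (1.96 + 0.84) × SE / √(1 − R²).

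| R² | n = 36 | n = 72 |
|---|---|---|
| 0 (unadjusted) | 1.00 SD | 0.95 SD |
| 0.1 | 1.06 SD | 1.00 SD |
| 0.3 | 1.20 SD | 1.13 SD |
| 0.5 | 1.42 SD | 1.34 SD |

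The model can be fitted. With an intercept, group, age and sex, the residual degrees of freedom are 10 + 36 − 4 = 42, or 10 + 72 − 4 = 78.

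**The case against.** The strongest reply is that this is an omission in a condensed article. The full protocol is not shown, and covariate handling for sequencing and metabolomic data is commonly left to an analysis plan. That is fair for the adjustment, and its absence alone would not be a finding. It carries less weight for recruitment: the article lists the control criteria in detail, a balancing rule belongs among them, and no analysis plan can restore balance once the volunteers have been chosen.

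Four stronger readings are tempting, and the document does not support them.

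- *A reader might infer that anyone aged 18 to 65 can be a control.* The symptom, GERD-Q and exclusion criteria also apply, and the age range equals the patients'.
- *A reader might infer that the comparison is confounded.* Neither group's age or sex mix is given, so only possible confounding can be claimed.
- *A reader might infer that 10 controls are too few to adjust.* Two covariates can be fitted with 42 residual degrees of freedom. The cost is small under mild imbalance (1.00 to 1.06 SD) and grows only as imbalance becomes severe. The main limit is the low precision of 10 controls, which is there before any adjustment and which matching does not cure.
- *A reader might quote error rates near 40%.* With d = 1.5 and r = 0.4 the formula gives 39% to 43%, but if both groups came from one population an age gap that large would have probability of about 0.003% (n = 36). It needs systematic selection by age, which no section describes.

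It is also true that the mechanistic outcome does not rest on the controls alone, since both randomised arms are sampled before and after treatment.

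**Conclusion.** The point holds in limited form. The control criteria share the patients' age range but leave the age and sex mix free, and the plan uses these non-randomised controls to identify flora and metabolite differences. Following it as written permits a confounded comparison; it does not show that one will occur.

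The inflation of the false-positive rate runs from negligible (about 6% at 0.5 SD and r = 0.2) to material (13% to 14% at 1 SD and r = 0.3), and depends wholly on the assumed age gap and correlation. Later adjustment is feasible but leaves detectable differences of 1.06 to 1.42 SD against 36 patients.

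Only the NERD-versus-healthy mechanistic comparison is concerned. The randomised comparison of the two arms and the GERD-Q primary outcome do not depend on the controls.

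**What to change.** Add to the inclusion criteria for healthy subjects that controls are recruited to match the sex ratio and coarse age distribution (for example two or three age bands) of the patients enrolled so far. Report age and sex of controls and patients side by side, and show an age- and sex-adjusted NERD-versus-healthy comparison as a sensitivity analysis.

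The bands should stay coarse. Sex by two or three bands gives 4 or 6 cells. Sex by 10-year band over 18 to 65 gives about 10 cells, roughly one control each, and adding body-mass bands would leave fewer controls than cells.

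The cost is slightly slower recruitment of 10 volunteers, because the patient mix has to be known first. No extra participants or tests are needed. If some controls have already been recruited, the rule can apply to the rest, and the side-by-side report and the sensitivity analysis remain available.
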